## 5 Study Population

### 5.1 Selection of the Study Population

Up to 10,000 healthy mother-infant pairs will be enrolled over a 4 year period. Infants will be between 6-14 weeks of age at enrollment and will be followed until they are 16 months of age. The goal is to maintain a continuous cohort of approximately 4,000 infants at any time, replacing those who go off study at 16 months of age with new subjects. Thus, study subjects will be infants, male or female, between the ages of 6 weeks to 16 months, of any race or ethnicity. The infants' mothers will also be included as study subjects (no age restriction). Infants with congenital medical conditions or born to HIV seropositive mothers (obtained by history) will be excluded so that these factors do not become confounding variables in the study. Pregnancy HIV testing will not be required. The study population will be drawn from infants born to mothers residing in the San Pablo City Health District, Laguna, Philippines. Study subjects will be recruited and enrolled in outpatient public health clinic settings.

### 5.2 Inclusion/Exclusion Criteria

#### *Inclusion Criteria for infants:*

- a) Infants born to mother residing in San Pablo Health District.
- b) Planned residence in San Pablo Health District for at least 1 year.
- c) Age 6-14 weeks\*.
- d) Informed consent.
- e) General good health

\* Except on study initiation, when over the first 5 months of Year 1 (est. Feb-June 2006), infants between the ages of 6-24 weeks will be allowed to enter the study).

#### *Exclusion Criteria for infants:*

- a) Infant born with congenital medical disorder.
- b) Mother known to be HIV seropositive.

Mothers of infants meeting the inclusion/exclusion criteria will also be enrolled, and this will include breastfeeding women. There are no requirements regarding contraception methods for the enrolled mothers.

## 6 STUDY PROCEDURES/EVALUATIONS

### 6.1 Study Procedures

Subjects will receive a study ID code identifying the sequence of enrollment. The alphanumeric study ID code will be generated automatically on the study database. A database linking identifying information with the study ID code will be maintained under restricted access, secure conditions, at RITM. Parents will receive a study ID card listing the infant's name, date of birth, and study ID code for use at future scheduled and surveillance study visits. Blood samples collected at scheduled or surveillance study visits will be identified by a different alphanumeric specimen ID code. Data will be recorded on paper case report forms (CRFs) appropriate to the study or surveillance visit. Blood sample collection data and diagnostic test results will also be recorded on paper CRFs. The data collection system will be compliant with all applicable regulations.

#### Time of participation

The expected total duration of an infants' participation is between 50-58 weeks, from the age of 6-14 weeks to 16 months. The total duration of the mothers' participation is one study visit upon study entry.

| Study visit             | Time required                      |
|-------------------------|------------------------------------|
| Study Visit #1 (infant) | 1.5 hours                          |
| Study Visit #1 (mother) | 1.5 hours (concurrent with infant) |
| Study Visit #2 (infant) | 1 hour                             |
| Study Visit #3 (infant) | 1 hour                             |

#### Data management

The paper CRFs will be kept in locked cabinets at the central field office, and first translated into electronic format (eCRFs) at the field office. The paper CRFs will then be transported to RITM for second data entry into eCRFs. This double data entry will serve as an initial quality assurance (QA) assessment. The need for continuation of double data entry will be re-assessed after 6 months. The eCRFs will be linked to the study database.

Analytic files will retain only the unique study ID code attached to each subject in the study. Data collection will follow a set of standard operating procedures that include field and office editing, and operation checks to ensure the validity of the data and adherence to the protocol. One electronic file will be created in MS Access for each CRF (including CRFs for diagnostic test results). CRFs will be re-abstracted at a rate of 1 in 20 in the field. Discordance will be noted and any apparent systemic errors at the field level will be investigated for possible needs to retrain staff. Data from the field will be submitted to the Data Management Unit at RITM for double encoding as noted earlier. After this initial check, a validation program

(developed by the programmer) will be run to check for inconsistencies in data. Initial tables are generated for final checking of data from CRFs before merging and analyzing databases.

The study database will be stored and maintained by the Data Management Unit at RITM. A back-up copy of validated data will be stored on CDs in a secure location at an external site. Back-up copies of validated data will also be sent to UMMS for secure storage. Data will be stored under secure conditions for a minimum of 10 years after completion of the study.

## 6.2 Laboratory Evaluations

### 6.2.1 Laboratory Evaluations/Assays

#### Scheduled Visits

| Time point              | Blood collection volume     | Aliquots/Assays                                                                                                                                                                      |
|-------------------------|-----------------------------|--------------------------------------------------------------------------------------------------------------------------------------------------------------------------------------|
| Study Visit #1 (infant) | 5 ml (anticoagulated tube)  | Plasma: 1.0 ml neut Ab assay, 1.0 ml ADE assay, 2.5 ml for repeat assays/storage (total 4.5 ml)
PBMC: $5 \times 10^6$ cells for activation and cytokine assays.                   |
| Study Visit #1 (mother) | 7 ml (serum separator tube) | Serum: 1.0 ml neut Ab assay, 2.0 ml for repeat assays/storage (total 3.0 ml)                                                                                                         |
| Study Visit #2 (infant) | 8 ml (anticoagulated tube)  | Plasma: 1.0 ml neut Ab assay, 1.0 ml ADE assay, 0.5 ml HAI assay, 2.0 ml for repeat assays/storage (total 4.5 ml)
PBMC: $8 \times 10^6$ cells for activation and cytokine assays. |
| Study Visit #3 (infant) | 5 ml (anticoagulated tube)  | Plasma: 0.5 ml HAI assay, 1.0 ml neut Ab assay, 2.5 ml for repeat assays/storage (total 4.0 ml)                                                                                      |

#### Surveillance (hospitalized or non-hospitalized dengue surveillance)\*

| Time point                             | Blood collection volume     | Aliquots/Assays                                                                                        |
|----------------------------------------|-----------------------------|--------------------------------------------------------------------------------------------------------|
| Acute illness sample                   | 3 ml (serum separator tube) | Serum: 0.25 ml IgM EIA, 0.25 ml RT-PCR, 1.0 ml for repeat assays/future RT-PCR and IgM/IgG EIA/storage |
| Convalescent sample (10-14 days later) | 3 ml (serum separator tube) | Serum: 0.5 ml for IgM/IgG EIA, 1.0 ml for repeat assays/storage                                        |

\* Participating infants cannot have > 2 paired (acute and convalescent) surveillance blood samples taken while in the study.

The proposed amount of blood drawn from study participants poses no more than minimal risk as defined by Office of Human Research Protections guidelines [19]. The amount of blood drawn does not exceed the lesser of 50 ml or 3 ml/kg in an 8 week period and collection does not occur more frequently than 2 times/week.

Assay descriptions:

**Virus RT-PCR-** A qualitative, serotype specific, DV RT-PCR assay will be performed on all acute illness serum samples. The assay technique has been previously published [23]. Results will be available within 3 days, and outpatient subjects with a positive DV RT-PCR will have a convalescent blood sample collected. Paired acute and convalescent serology will be performed to confirm primary DV infections (see below).

**Serology-** An anti-DV IgM EIA will be done on all acute illness serum samples collected. The results will be available within 3 days, and outpatient subjects with a positive DV IgM will have a convalescent blood sample collected. Paired acute and convalescent sera will be tested for anti-DV IgM/IgG by EIA using standard techniques and criteria to confirm primary DV infections [24].

At the conclusion of the year, plasma samples from the 250 subjects with 3 scheduled study visits will be identified. These subjects will not have had an earlier recognized symptomatic DV infection. The plasma samples that span a significant part of the peak DV transmission season will be tested for anti-DV Abs by HAI serology [25] to identify those with clinically unrecognized seroconversions.

**Neutralizing Ab assays-** All subjects in the clinical study with evidence of DV infection (Categories I-IV) will have neutralizing anti-DV Ab titers determined in their pre-infection blood draw. The neutralizing Ab titers will be determined using a standard plaque reduction assay to reference DV isolates serotypes 1-4 [13]. We have previously shown that neutralizing Ab titers to reference DV isolates correlate well with neutralizing Ab titers to the actual infecting virus isolate [13]. The 50% plaque reduction neutralization titer will be calculated using 4-parameter curve fitting analysis.

**Peak viremia determinations-** We have found that viremia levels obtained within 72 hours of symptom onset in dengue are a good approximation of peak viremia levels [20-22]. A serotype specific, fluorogenic, quantitative RT-PCR assay will be performed on the acute illness serum samples collected within 72 hours of symptom onset from infants in Categories I-III.

**Ab-dependent enhancement of infection assay (ADE)-** All subjects in the clinical study with evidence of DV infection or likely exposure (Categories I-IV) will have an ADE Ab assay performed using their pre-infection blood draw.

**PBMC activation-** We recognize that limited numbers of PBMC will be available for study from the infant blood draws. Therefore, we plan to use modern multiplex assay techniques to get an overview of DV-induced immune activation patterns in infant PBMC. We will first perform the assays on serial collected PBMC (study visits 1 and 2) from 30 subjects without evidence of DV infection (Category V). This will allow us to refine the assays. Once optimized, the assays will be done on the pre-infection PBMC from all subjects with evidence of DV infection (Categories I-IV).

PBMC will be stimulated in vitro with DV and controls. At the early and late time points, cell culture supernatants will be collected and cellular RNA will be isolated. Pro- and anti-inflammatory cytokine/chemokine levels will be determined in the supernatants using a multiplex bead assay. 9 cytokines/chemokines will be assayed in a single sample using the preconfigured panel shown below:

| Category                    | Mediators                                                      |
|-----------------------------|----------------------------------------------------------------|
| Pro-inflammatory mediators  | IL-1 $\beta$ , IL-6, TNF- $\alpha$ , IFN- $\gamma$ , IL-12 p70 |
| Anti-inflammatory mediators | IL-4, IL-10, IL-13                                             |
| CC chemokines               | MCP-1                                                          |

Regulation of vascular permeability is an important factor in DHF pathogenesis, and modulation of anti-viral and antigen-presentation functions are well established paradigms in many virus-host interactions. We will use cellular RNA to investigate these additional immune response gene expression profiles by quantitative, real-time, fluorogenic RT-PCR. Gene expression levels will be compared to established housekeeping genes. The genes to be investigated are shown below:

| Category                        | Gene profiles                      |
|---------------------------------|------------------------------------|
| Vascular permeability mediators | TXAS, HIF-1 $\alpha$ and VHL, VEGF |
| Anti-viral activities           | OAS2, OASL, MX1, ISG15             |
| MHC Class I antigen processing  | PSMA2, $\beta$ 2M, TAPBP           |
| MHC Class II antigen processing | CIITA, li                          |

The strategy outlined above will allow us to investigate different relevant aspects of the infant response to DV infection with limited sample volumes and cell numbers.

*IFN- $\gamma$  enzyme-linked immunoSPOT*- Although pre-existing DV T-cell reactivity is not expected in infants with primary DV infections, potential T-cell responses to DV will be examined as part of the comprehensive assessment of DHF risk factors. There is limited literature suggesting that maternal T-lymphocytes may be transferred to infants by breastfeeding [26, 27]. We will first perform the assay on serial collected PBMC (study visits 1 and 2) from 20 breastfed infants without evidence of DV infection (Category V) and born to DV-seropositive mothers. This will allow us to see if indeed DV-reactive T-cells are detectable, and, if so, investigate possible age-related changes. Then, the assay will be done on the remaining 2-3x10^6 pre-infection PBMC from the subjects with evidence of DV infection (Categories I-IV).

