## **2.3 Potential Risks and Benefits**

### **2.3.1 Potential Risks**

#### **a) Phlebotomy –**

- Immediate risks- can infrequently cause temporary bruising, erythema, pain, infection, or bleeding.
- Long range risks- none.
- Rationale- There are no direct health benefits from the collection of blood samples to the subjects. The minimal risks of phlebotomy are reasonable and necessary to successfully address the study objectives, namely identify immunological correlates of protection to dengue.
- To diminish the risk of phlebotomy, only adequately trained study personnel will draw blood. Blood volumes taken from the study subjects fall within the Office of Human Research Protections guidelines for minimal risk studies [19]. Alternative procedures are not feasible.

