### II. Scheduled visits

- i) Study Visit #1/Study entry- Mothers and infants will enter the study when the infant is between the ages of 6-14 weeks\*. We anticipate that the majority of infants will enter the study at ages 6, 10, or 14 weeks, when they are scheduled for one of their Extended Programme in Immunization (EPI) vaccinations (diphtheria/pertussis/tetanus, polio). After informed consent is obtained, data on the mother and the birth will be collected. In all infants, an anticoagulated blood sample will be collected upon study entry for plasma and peripheral blood mononuclear cells (PBMC) isolation. A serum sample from the mother will be collected at the same time or within 2 weeks of the infant blood sample.  
(\* Except on study initiation, when over the first 5 months of the study, infants between the ages of 6-24 weeks will be allowed to enter the study. This is to achieve an adequate sized study cohort for surveillance during the first dengue season).

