**Data on infants to be collected**

|                |                                                                                                                                              |
|----------------|----------------------------------------------------------------------------------------------------------------------------------------------|
| Form data      | Date, Study ID no, subject initials, Study Visit #                                                                                           |
| Demographics   | Name, age, date of birth, gender                                                                                                             |
| Past med hx    | Hospitalization between birth and current visit, reason, and location?
Febrile illnesses lasting >3 days between birth and current visit? |
| Medications    | Current medications                                                                                                                          |
| Measurements   | Height, weight, temperature                                                                                                                  |
| Vaccination hx | Vaccinations received to date from EPI card                                                                                                  |

- ii) Study Visit #2- Study Visit #2 will take place when the infant is between the ages of 4-6 months. At this time, data on infant health will be obtained. In all infants, an anticoagulated blood sample will be collected for plasma and PBMC isolation.

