**Data on infants to be collected**

|                |                                                                                                                            |
|----------------|----------------------------------------------------------------------------------------------------------------------------|
| Form data      | Date, Study ID no, subject initials, Study Visit #                                                                         |
| Demographics   | Date of birth, gender                                                                                                      |
| Past med hx    | Hospitalization since last study visit, reason, and location?
Febrile illnesses lasting >3 days since last study visit? |
| Medications    | Current medications                                                                                                        |
| Measurements   | Height, weight, temperature                                                                                                |
| Vaccination hx | Vaccinations since last study visit from EPI card                                                                          |
| Feeding        | Breastfeeding alone, breastfeeding+formula/solids, formula/solids alone; if breastfeeding, quantify times/24 h period.     |

- iii) Study Visit #3- At age 15-16 months, 250 infants/year will be selected to return for a 3rd study visit. The 250 infants will be randomly selected from those without prior symptomatic dengue and whose study visits 2 and 3 span a significant portion of the peak DV transmission season (June-October). Data on infant health will be obtained and an anticoagulated blood sample for plasma will be collected.

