**Data on infants to be collected**

|                |                                                                                                                            |
|----------------|----------------------------------------------------------------------------------------------------------------------------|
| Form data      | Date, Study ID no, subject initials, Study Visit #                                                                         |
| Demographics   | Date of birth, gender                                                                                                      |
| Past med hx    | Hospitalization since last study visit, reason, and location?
Febrile illnesses lasting >3 days since last study visit? |
| Medications    | Current medications                                                                                                        |
| Measurements   | Height, weight, temperature                                                                                                |
| Vaccination hx | Vaccinations since last study visit from EPI card                                                                          |
| Feeding        | Breastfeeding alone, breastfeeding+formula/solids, formula/solids alone; if breastfeeding, quantify times/24 h period.     |

III. Surveillance

- i) Hospitalized dengue- Surveillance for DV infections that result in hospitalization will occur year round and throughout the entire period of an infant's study participation (ages 6 weeks-16 months). Upon study enrollment, parents will be given a study identification card that will have their infant's unique identification number. When any infant in the study presents to one of the 7 hospitals serving San Pablo City, they will be identified as a study participant and their identification number and date/time of presentation will be transmitted to the study coordinating center at the City Health Office. Study personnel will then screen infants in the study who were admitted for acute febrile illnesses. Those infants will have history and clinical data abstracted, and an acute illness blood sample (serum) taken for dengue diagnostic testing. A convalescent blood sample (serum) will also be taken 10-14 days later.

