**Data to be collected on infants hospitalized with acute febrile illnesses**

|                 |                                                                                                      |
|-----------------|------------------------------------------------------------------------------------------------------|
| Form data       | Date, Study ID no, subject initials, location code                                                   |
| Demographics    | Date of birth, gender                                                                                |
| Illness type    | Fever onset, symptoms, signs                                                                         |
| Hospital course | Clinical, laboratory, and radiographic data abstracted from medical record at end of hospitalization |

- ii) Non-hospitalized dengue- Each year during the peak DV transmission season from June to October, we will also conduct surveillance for DV infections that do not result in hospitalizations. During this time period, parents will be encouraged to bring their infants to the barangay health stations, local doctor's offices, or the City Health office if they develop an acute febrile illness. We will rely primarily on parents bringing their infants to the City Health office for febrile illnesses during the peak dengue season. In addition, nearly all pediatric health care providers in San Pablo will be aware of the study through education and information distributed through the local medical society and hospitals. Parents will be

reminded to present their study identification cards if they bring their infant with a fever > 38.0°C to a barangay health station or a private doctor's office. The health care personnel will be instructed to call a central telephone number where study personnel will coordinate transportation to the City Health office. There, study personnel will assess the infants, complete a questionnaire, and obtain an acute illness blood specimen (serum) for dengue diagnostic testing in addition to any routine clinical tests that may be requested by the treating nurse or physician. If the acute illness serum sample returns positive by DV IgM or RT-PCR, study personnel will arrange for collection of a convalescent blood specimen (serum) 10-14 days later.

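### The 3 ml/kg blood-draw limit in Section 6.2.1 is stated as met, but the fixed volumes and visit windows do not ensure it: 19 ml in 8 weeks is possible, over the limit below 6.33 kg

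*Protocol*

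**What the plan says.** Section 6.2.1, below the surveillance table, supports the minimal-risk classification with an unconditional statement: "The amount of blood drawn does not exceed the lesser of 50 ml or 3 ml/kg in an 8 week period". Section 2.3.1 repeats it in general terms: "Blood volumes taken from the study subjects fall within the Office of Human Research Protections guidelines for minimal risk studies".

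The tables in 6.2.1 fix the infant draws at 5 ml (Visit 1), 8 ml (Visit 2), and 3 ml for each acute and each convalescent sample. None depends on weight, and the eligibility criteria in 5.2 set no minimum weight.

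Timing is in Section 4. Entry is at 6-14 weeks, with this expectation: "We anticipate that the majority of infants will enter the study at ages 6, 10, or 14 weeks". During start-up, Section 5.2 says "infants between the ages of 6-24 weeks will be allowed to enter the study". For the second draw, "Study Visit #2 will take place when the infant is between the ages of 4-6 months".

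For hospital admissions with any acute febrile illness, year round, an acute sample is drawn and "A convalescent blood sample (serum) will also be taken 10-14 days later". Outpatient surveillance runs June-October, and the convalescent draw there requires a positive RT-PCR or IgM.

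Two other limits are stated: no more than two surveillance pairs over the whole study, and no more than two collections a week.

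**The concern.** The limit is per kilogram and per 8 weeks, but nothing that controls the draws is expressed in those terms. The two-pair cap counts pairs over about a year, and the frequency limit does not restrict total volume. Staff who follow every listed volume and window exactly can therefore exceed a limit that the protocol says is not exceeded.

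Most of the information for a check is already collected. Weight is measured at the scheduled visits, the Visit 2 form asks about "Hospitalization since last study visit, reason, and location", and each draw is logged. No instruction combines these into a volume check. At illness visits the weight itself may be missing. The hospital form names no weight field, and its course data are "Clinical, laboratory, and radiographic data abstracted from medical record at end of hospitalization", which is after the acute draw. The fields of the outpatient questionnaire are not listed.

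At stake is a safety assurance for infants, not an analysis.

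**Working it through.** **Inputs.** Limit: the lesser of 50 ml or 3 ml/kg per 8 weeks (6.2.1). Volumes: 5, 8, 3 and 3 ml (6.2.1). Entry: 6-14 weeks, or 6-24 weeks at start-up. Visit 2: 4-6 months (Section 4). Convalescent draw: 10-14 days after the acute draw.

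**Which arm of the limit binds.** 50/3 = 16.67 kg, so below that weight 3 ml/kg is the operative limit.

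**When both visits fit in 8 weeks.** One month is 365.25/12/7 = 4.348 weeks.
- Visit 2 window: 4 × 4.348 = 17.4 weeks to 6 × 4.348 = 26.1 weeks.
- Earliest entry age that allows overlap: 17.4 − 8 = 9.4 weeks (8.0 weeks if 4 months is read as 16 weeks).
- Entry at 6 weeks: the 8 weeks end at 14.0 weeks, so there is no overlap.
- Entry at 14 weeks: overlap if Visit 2 falls between 17.4 and 22.0 weeks. The smallest gap is 17.4 − 14 = 3.4 weeks, which leaves room for a pair drawn 10-14 days apart.
- Entry after 26.1 − 8 = 18.1 weeks (start-up only): overlap cannot be avoided within the Visit 2 window.

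**Volume and the weight needed to comply (volume/3).**

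| Draws within 8 weeks | Total | Complies from |
|---|---|---|
| Visits 1 + 2 | 5 + 8 = 13 ml | 4.33 kg |
| Visits 1 + 2 + acute only (dengue-negative outpatient) | 13 + 3 = 16 ml | 5.33 kg |
| Visits 1 + 2 + one pair (any febrile admission, or dengue-positive outpatient) | 13 + 6 = 19 ml | 6.33 kg |
| Visit 2 + two pairs (any entry age) | 8 + 12 = 20 ml | 6.67 kg |
| Visits 1 + 2 + two pairs (permitted, should be rare) | 13 + 12 = 25 ml | 8.33 kg |

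**At assumed weights.** The protocol gives no infant weights. At 5, 6 and 7 kg the allowance is 15, 18 and 21 ml. A total of 19 ml exceeds it at 5 kg (3.80 ml/kg) and 6 kg (3.17 ml/kg), but not at 7 kg (2.71 ml/kg).

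**The case against.** **The sentence is itself the rule.** It stands beside two operating limits, so a draw that broke it would be a deviation, and Section 6.1 refers to standard operating procedures with operation checks on adherence. That reading is possible. But the surrounding text describes the proposed volumes and uses the limit to justify minimal risk. If it is meant to bind, staff have fixed volumes that can conflict with it and no instruction on which draw gives way. The checks in 6.1 concern data collection, and none described there is made before a draw.

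**The coincidence is uncommon.** Outpatients give a convalescent sample only after a positive test and only in season, and Section 7.2 expects 44 such cases in four years. Section 2.1 places most infant DHF at 6-9 months, largely after the Visit 1-2 interval. This stands: it would be wrong to treat every febrile illness as a 6 ml pair. The hospital route, however, needs no dengue diagnosis and runs all year, and the protocol gives no count of febrile admissions.

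**The infants may be heavy enough.** When the total includes Visit 2, the infant is at least 17.4 weeks old by that draw, and was in good health at entry. This also stands as a limit on the point: the protocol does not say how many infants at that age are below 6.33 kg.

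**Conclusion.** The point holds as a gap between a stated safety property and the design that is meant to deliver it. Following the tables exactly can give 19 ml in 8 weeks, over the limit below 6.33 kg, and up to 20 ml (6.67 kg) whatever the entry age. An excess needs an illness draw close to the scheduled visits and a low enough weight; the 19 ml case also needs entry from about 9.4 weeks. No endpoint or analysis is affected. The change is worth making because it is cheap and protects infants.

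A reader might infer three stronger things that the document does not support.
- That the routine schedule breaks the limit: 13 ml complies from 4.33 kg.
- That overlap shares are probabilities. For entry at 14 weeks, (22.0 − 17.4)/8.7 = 53% of the Visit 2 window lies within 8 weeks of Visit 1. That is a share of a window, not a chance: nothing says visits are spread evenly over it, and it covers only the 13 ml case.
- That a breach rate can be given: weights and febrile admission counts are absent.

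**What to change.** Add one paragraph to 6.2.1 making 3 ml/kg an operative cap.
- Record weight at every illness visit, before the draw.
- Before each research draw, total that infant's research volume over the previous 8 weeks and compare it with 3 ml/kg at current weight.
- If the cap would be exceeded, keep the acute diagnostic sample. Take a smaller Visit 2 draw, or move it later within the 4-6 month window.
- Take the convalescent sample on time at 10-14 days but at reduced volume, dropping its storage share (1.0 of 1.5 ml serum). Do not defer it, because the paired sample confirms primary infection.

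As an illustration, assume serum yield scales with blood volume. The convalescent cut then saves 3 × 1.0/1.5 = 2.0 ml, so 19 ml becomes 17 ml (5.67 kg). That is enough at 6 kg (18 ml); at 5 kg (15 ml), Visit 2 would also have to fall from 8 to 6 ml. No matching saving should be worked out for Visit 2 from its plasma aliquots, because the table shows 4.5 ml plasma from both a 5 ml and an 8 ml draw.

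Moving Visit 2 more than 8 weeks after Visit 1 leaves Visit 2 plus one pair at 14 ml (4.67 kg). It does not replace the check, since Visit 2 plus two pairs is still 20 ml. The paragraph should also say what happens if Visit 2 has already been drawn when a smaller infant falls ill, because only the illness samples can then be adjusted.

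Cost: a weight entry, a running total from draws already logged, and an occasional smaller or later Visit 2 sample. That means fewer PBMC (about 6 million from 6 ml at the table's 1 million per ml) and less stored plasma or serum. If an illness falls within the delay, Visit 1 is the only pre-illness sample, so a smaller draw may be preferable to a later one.
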